## CRF content confirmation and inquiries

1. The data center will verify the following items for the entered CRF and centralized testing results (blood biomarkers, urinary biomarkers).
2. Input errors
3. Consistency with the current research plan
4. Consistency of CRF contents
5. Outliers in blood and urinary biomarkers
6. The data center will compile the points to be inquired about and send a data inquiry form to the principal investigator by email or via EDC.
7. The principal investigator, co-investigator, or research collaborator will promptly enter or modify the CRF on the EDC and notify the data center if no modification is required in response to the inquiry.

# **Inclusion criteria**

## Study participants

Patients with CKD and type 2 diabetes

## Inclusion criteria

Patients who meet all of the following criteria are eligible:

1. Patients who provide written informed consent to participate in this study
2. Patients aged ≥ 20 years at the time of consent (regardless of sex)
3. Patients with type 2 diabetes
4. Patients with CKD meeting both the following criteria:
   1. eGFR, 25–90 mL/min/1.73 m^2^

II. UACR, 30–3500 mg/g.cr.

1. Patients who have not changed their medication for type 2 diabetes or CKD in the 4 weeks prior to providing consent

Inclusion criteria rationale:

1. This was set to comply with the Clinical Research Act.
2. This was set to target people aged ≥ 20 years who can individually provide consent.

3) to 5) were set to select cases that met the objectives of this study.

## Exclusion criteria

Patients who meet any of the following criteria will be excluded from this study:

1. Patients currently on MRA, including finerenone, or those who have been administered it within the 4 weeks prior to providing informed consent
2. Patients with a history of hypersensitivity to finerenone
3. Patients with HbA1c ≥ 10%
4. Patients with serum potassium levels ≥ 4.9 mEq/L
5. Patients with NYHA class II–IV HFrEF (LVEF ≤ 35%)
6. Patients with poorly controlled hypertension including those with systolic blood pressure ≥ 170 mmHg, diastolic blood pressure ≥ 110 mmHg, and hypertensive emergency
7. Patients with a history of ischemic stroke, acute coronary syndrome, cardiovascular surgery or percutaneous treatment, or hospitalization due to worsening heart or renal failure within the 8 weeks prior to providing consent
8. Patients scheduled to undergo coronary revascularization or other surgical or percutaneous treatment for cardiovascular disease during the observation period
9. Patients scheduled to undergo treatment, including electrical defibrillation, cardiac resynchronization therapy, or pacemaker implantation, during the observation period
10. Patients scheduled to undergo dialysis or kidney transplantation during the observation period
11. Patients with severe liver dysfunction (Child-Pugh class C)
12. Patients administered itraconazole, ritonavir-containing preparations, atazanavir, darunavir, fosamprenavir, cobicistat-containing preparations, or clarithromycin
13. Patients with Addison’s disease
14. Patients with active infectious disease
15. Patients with pregnancy, possibly pregnancy, or breastfeeding
16. Patients deemed unsuitable for this study by the principal investigator or co-investigator including patients with renal artery stenosis, one kidney, and active malignant tumor

Exclusion criteria rationale:

1), 8) to 10) were set owing to their expected impact on the endpoints.

2) to 4) and 11) to 15) were set to ensure patient safety.

5) This was set because the guidelines recommend the administration of MRA, the same type of drug as the study drug.

6) and 7) were set because of their expected impact on ensuring patient safety and on the endpoints.

16) This was set assuming that the principal investigator and/or co-investigator would decide the suitability of a patient as a participant from a scientific and ethical perspective.

## Discontinuation criteria for study participants

The study will be discontinued for the circumstances mentioned below. If it is discontinued, the reason and the discontinuation date will be entered in the CRF. If the discontinuation date is within the 4-, 12-, or 24-weeks allowance, tests will be performed to the extent possible.

1. A study participant declines to participate in the study or withdraws consent.
2. Patient transfer to another hospital makes visiting the medical institution where the study is being conducted difficult for the participant.
3. Discovery of a participant not meeting the inclusion criteria or meeting the exclusion criteria after the study initiation.
4. The principal investigator or co-investigator determines that continuation of the study is difficult owing to the occurrence of an adverse event.
5. The principal investigator or co-investigator determines that continuation of the study is difficult owing to worsening of a primary disease or complications.
6. The study is unlocked.
7. The principal investigator or co-investigator determines it is appropriate to discontinue participation in the study for other reasons.

## Treatment of study participants discontinuing the study

For study participants discontinuing, except those under conditions 1–4 mentioned below, a discontinuation examination will be performed to the extent possible, and they will cease to participate in the study. For the examination schedule, refer to the relevant section of “observation and testing items.” Even if the observations specified in the research plan cannot be carried out owing to reasons including transfer to another hospital, outcome information will be obtained from the transferred hospital to the extent possible, and the obtained information will be included in the medical records including the chart along with the method and date of acquisition.

1. The study participant dies
2. The study participant withdraws consent for follow-up after discontinuation
3. The study participant is discovered to be ineligible after study initiation
4. Tracking the participant is difficult for other reasons

# **Treatment of the study participants**

## Observation and testing schedule

The observation and testing items and schedule for this study are presented below. The study investigators will conduct observation and testing according to the schedule. However, for tasks that can be completed by research collaborators, including obtaining patient background data and conducting clinical tests, the research collaborators may perform them under the supervision of the principal investigator or co-investigator.

Table 1. Observation and testing schedule

| Timing  Testing item | Consent  acquisition | Eligibility determination,  registration, and allocation | Observation period ^1)^ | | | |
| --- | --- | --- | --- | --- | --- | --- |
|  |  |  | Baseline ^2) 3)^ | Week 4 | Week 12 | Week 24 |
|  |  |  | Day 0 | Day 28  [21–35] | Day 84  [70–98] | Day 168  [154–182] |
| Obtaining consent | ● |  |  |  |  |  |
| Eligibility determination, ^4)^ Information required for registration and allocation ^5)^ |  | ● |  |  |  |  |
| Patient background information |  | ● |  |  |  |  |
| Physical examination findings ^6)^ |  |  | ● | ● | ● | ● |
| CAVI |  |  | ● |  |  | ● |
| UACR |  |  | ●^7）^ |  | ● | ● |
| Serum creatinine, eGFR, serum cystatin C |  |  | ●^7）^ | ●^8)^ | ● | ● |
| Other biomarkers (blood and urine) ^9,10)^ |  |  | ● |  |  | ● |
| Proteomics ^10)^ |  |  | ● |  |  | ● |
| Blood test ^11)^ |  |  | ●^12)^ | ●^13)^ | ●^14)^ | ●^15)^ |
| Cardiac ultrasound examination ^16)^ |  |  | ●^17)^ |  |  | ● |
| Concomitant medications ^18)^ |  |  | ● |  |  | ● |
| Compliance with the study drug |  |  |  |  |  |  |
| Adverse events |  |  |  |  |  |  |

[ - ]: Allowance range

1) If the discontinuation date is within the 4-, 12-, or 24-weeks allowance, observations and tests will be conducted to the extent possible.

2) In principle, a baseline test will be conducted within 60 days of obtaining consent, and administration of the study drug will begin the next day.

3) If eligibility determination and baseline are conducted on the same day, the same data can be used for overlapping items.

4) When determining eligibility, the eGFR, UACR, HbA1c, serum potassium, and LVEF levels will also be recorded and entered into the EDC. Data obtained after obtaining consent will be prioritized for eGFR, UACR, and LVEF levels; however, in the absence of this information, data obtained within 3 months prior to obtaining consent can be used.

5) At the time of registration and allocation, data on date of consent, age at the time of providing consent, date of birth, sex, use of SGLT2 inhibitors, and eGFR will be recorded. For eGFR, data obtained after obtaining consent will be prioritized; however, in the absence of this information, data from within 3 months prior to consent can be used.

6) Height (data obtained after obtaining consent will be prioritized; however, in the absence of this information, data from within 3 months prior to consent can be used. Height will only be measured at baseline.), weight, blood pressure (clinic/home*), and pulse rate (clinic/home*).

^*Optional.^

7) For UACR and serum cystatin C, baseline data will be prioritized; however, if the baseline data is unavailable, data within 3 months from the baseline may be used.

8) Serum creatinine and eGFR only.

9) Blood (pentosidine) and urine (type IV collagen, α1-MG, β2-MG, NGAL, NAG, and L-FABP creatinine ratio).

10) Measurement will be outsourced.

11) Hemoglobin, hematocrit, serum albumin, serum potassium, HbA1c, plasma aldosterone concentration, plasma renin activity

12) HbA1c, data obtained after obtaining consent will be prioritized; however, in the absence of this information, data at the time of eligibility determination may be used.

13) Only serum potassium levels are measured.

14) Only serum potassium and HbA1c levels are measured.

15) Only serum potassium and HbA1c levels, plasma aldosterone concentration, and plasma renin activity are measured.

16) This is an optional item.

17) Baseline data will be prioritized; however, if the baseline data is unavailable, data within 3 months from the baseline may be used.

18) In principle, no new administration of SGLT2 inhibitors and no changes in the dosage and administration of concomitant medications will be implemented during the observation period.

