## Research methodology (clinical research procedures)

After verifying the eligibility of patients who have provided written consent, patients who meet all inclusion criteria will be enrolled in the study. Patients will be randomized (allocated) to either the finerenone or placebo groups. They will undergo double-blind administration and observation at baseline (before the start of administration of the study drug) and at 4, 12, and 24 weeks after protocol treatment initiation, as well as prescribed tests (Figure). In principle, baseline tests will be conducted within 60 days of obtaining consent, and study drug administration will begin the following day.

[figure not shown]

Figure (from Tanaka et al. Cardiovasc Diabetol. 2023;22:194)

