## Scheduled observation and testing items

1. Baseline (Day 0)

In principle, a baseline test will be conducted within 60 days of obtaining consent, and administration of the study drug will begin the next day. If eligibility determination and baseline are conducted on the same day, the same data can be used for overlapping items.

1. Physical examination findings:

Height*, weight, clinic blood pressure (systolic and diastolic), clinic pulse rate

Optional: Home blood pressure (systolic and diastolic), home pulse rate

1. CAVI:

The device that measures CAVI (Basera) is approved as a medical device (blood pressure pulse wave inspection device) and is used to measure non-invasive blood pressure, electrocardiogram, phonocardiogram, and pulse wave chart to test arterial distensibility or blood flow disorder in the blood vessels of the lower limbs. Measurements are performed with reference to Appendix 2 (Basera Test Guide).

1. UACR** levels
2. Serum creatinine, eGFR, serum cystatin C** levels
3. Other biomarkers: (Outsourced measurement)

Blood (Pentosidine)

Urine (type IV collagen, α1-MG, β2-MG, NGAL, NAG, and L-FABP creatinine ratio).

1. Proteomics (outsourced measurement)
2. Blood tests:

Hemoglobin, hematocrit, serum albumin and potassium levels, HbA1c***, plasma aldosterone concentration, plasma renin activity

1. Cardiac ultrasound examination (optional)****:

LVEF, septal e′, lateral e′, mitral orifice blood flow velocity waveform (E), E/e′, LVMI, LAVI

1. Concomitant medications:

ACE inhibitors, ARBs, ARNIs, β-blockers, calcium antagonists, diuretics, statins, insulin, metformin, SGLT2 inhibitors, GLP-1 receptor agonists, DPP-4 inhibitors, iron preparations, ESAs, HIF-PH inhibitors, and hyperkalemia medications

During the observation period, in principle, no new administration of SGLT2 inhibitors and no changes in the dosage and administration of concomitant medications will be implemented.

* Data obtained after obtaining consent will be prioritized; however, in the absence of this information, data from within 3 months prior to consent can be used.

**Baseline data will be prioritized; however, if the baseline data is unavailable, data within 3 months from the baseline may be used.

*** Baseline data will be prioritized; however, if the baseline data is unavailable, data from the time of eligibility determination may be used.

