**** Baseline data will be prioritized; however, if the baseline data is unavailable, data from 3 months prior to obtaining consent up to baseline may be used.

1. Week 4 (Day 28, allowable range for observation and testing: Days 21–35)
2. Physical examination findings:

Weight, clinic blood pressure (systolic and diastolic), clinic pulse rate

Optional: Home blood pressure (systolic and diastolic), home pulse rate

1. Serum creatinine levels and eGFR
2. Blood test: serum potassium levels
3. Week 12 (Day 84, allowable range for observation and testing: Days 70–98)
4. Physical examination findings:

Weight, clinic blood pressure (systolic and diastolic), clinic pulse rate

Optional: Home blood pressure (systolic and diastolic), home pulse rate

1. UACR levels
2. Serum creatinine, eGFR, serum cystatin C levels
3. Blood tests: serum potassium and HbA1c levels
4. Week 24 (Day 186, allowable range for observation and testing: Days 154–182)
5. Physical examination findings:

Weight, clinic blood pressure (systolic and diastolic), clinic pulse rate

Optional: Home blood pressure (systolic and diastolic), home pulse rate

1. CAVI:
2. The device that measures CAVI (Basera) is approved as a medical device (blood pressure pulse wave inspection device) and is used to measure non-invasive blood pressure, electrocardiogram, phonocardiogram, and pulse wave chart to test arterial distensibility or blood flow disorder in the blood vessels of the lower limbs. Measurements are performed using Appendix 2 (Basera Test Guide) as a reference.
3. UACR levels
4. Serum creatinine, eGFR, serum cystatin C levels
5. Other biomarkers: (Outsourced measurement)

Blood (Pentosidine)

Urine (type IV collagen, α1-MG, β2-MG, NGAL, NAG, and L-FABP creatinine ratio).

1. Proteomics (outsourced measurement)
2. Blood tests:

Serum potassium and HbA1c levels, plasma aldosterone concentration, plasma renin activity

1. Cardiac ultrasound examination (optional):

LVEF, septal e′, lateral e′, mitral orifice blood flow velocity waveform (E), E/e′, LVMI, LAVI

1. Concomitant medications:

ACE inhibitors, ARBs, β-blockers, calcium antagonists, diuretics, statins, insulin, metformin, SGLT2 inhibitors, GLP-1 receptor agonists, DPP-4 inhibitors, iron preparations, ESAs, HIF-PH inhibitors, and hyperkalemia medications

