| **4. Treatment of the study participants**  **4.1. Observation and examination schedule**  Table 1. Observation and examination schedule  7) For UACR and serum cystatin C, baseline data will be prioritized; however, if baseline data is unavailable, data within 3 months from the baseline may be used. | **4. Treatment of the study participants**  **4.1. Observation and examination schedule**  Table 1. Observation and examination schedule  7) For UACR and serum cystatin C, baseline data will be given prioritized; however, if baseline data is unavailable, data from within 3 months prior to the baseline may be used. | Correction |
| **4. Treatment of the study participants**  **4.1. Observation and examination schedule**  Table 1. Observation and examination schedule  11) Hemoglobin, hematocrit, serum albumin, serum potassium, HbA1c, plasma aldosterone concentration, plasma renin activity  15) Only serum potassium, HbA1c, plasma aldosterone concentration, and plasma renin activity will be measured. | **4. Treatment of the study participants**  **4.1. Observation and examination schedule**  Table 1. Observation and examination schedule  11) Hemoglobin, hematocrit, serum albumin, serum potassium, HbA1c, plasma (or serum is also acceptable) aldosterone concentration, plasma (or serum is also acceptable) renin activity or concentration  15) Only serum potassium, HbA1c, plasma (or serum is also acceptable) aldosterone concentration, and plasma (or serum is also acceptable) renin activity or concentration will be measured. | Added information |
| **4. Treatment of the study participants**  **4.2. Patient enrollment**  2) Based on the results of the eligibility assessment, the eligibility and allocation test items will be entered into the EDC, and registration and allocation will be performed. A patient identification number will be assigned to registered study participants (including those determined as "ineligible" by the EDC), and the group to which they were assigned will be displayed for eligible cases. | **4. Treatment of the study participants**  **4.2. Patient enrollment**  2) Based on the results of the eligibility assessment, the eligibility and allocation test items will be entered into the EDC, and registration and allocation will be performed. A patient identification number will be assigned to the registered study participants (including those determined as "ineligible" by the EDC), and a "study drug number" will also be displayed. | Typo |

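### Table 1 footnote 17 and the section 4.3 note give conflicting fallback windows for the baseline echocardiogram, and footnote 17 does not exclude a scan taken after the first dose

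*Combined protocol and SAP*

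**What the plan says.** The protocol states the fallback for a missing baseline echocardiogram twice, in different terms.

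- **Section 4.1, Table 1, footnote 17** (attached to the baseline cardiac ultrasound): "17) Baseline data will be prioritized; however, if the baseline data is unavailable, data within 3 months from the baseline may be used".
- **Section 4.3, Baseline (Day 0), four-asterisk note** (attached to the item "Cardiac ultrasound examination (optional"): "if the baseline data is unavailable, data from 3 months prior to obtaining consent up to baseline may be used".

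Three other statements bear on how these are read.

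- **Timing of the first dose.** Section 4.3 says that after the baseline test, in principle, "administration of the study drug will begin the next day".
- **Meaning of baseline.** The section on clinical research procedures speaks of "observation at baseline (before the start of administration of the study drug".
- **Precedent.** Footnote 7 used the same wording for two laboratory measures, in a sentence that begins: "7) For UACR and serum cystatin C, baseline data will be prioritized; however, if the baseline data is unavailable, data within 3 months from the". The version 1.1 to 1.2 comparison table changed it to "data from within 3 months prior to the baseline may be used" and gave the reason as a correction. The matching note in section 4.3 was changed in the same way. None of the three comparison tables changes footnote 17 or the four-asterisk note.

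The SAP reports no changes from the research plan. It defines change as the value at time t minus the baseline value (Defining calculation items), with no date window for the latter. It also uses the baseline value as covariate in the echocardiographic models (Analysis of other endpoints).

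**The concern.** Two rules for one examination cannot both be followed, and they differ in whether an on-treatment measurement can count as a baseline. A scan made on finerenone may already carry part of the drug's effect. If it is entered as the baseline, that part is removed from the change to week 24, and the treatment difference moves toward zero. The week-24 changes in LVEF, septal and lateral e′, E, E/e′, LVMI, LAD and LAVI are the endpoints at stake. The SAP contains no check that would catch such a value.

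**Working it through.** **Stated design figure.** The plan gives no figure for the echocardiographic endpoints. Its only design figure is the sample size for CAVI. With 0.6 SD, two-sided 5% and 80% power, a two-sample t-test needs 44.6, so 45 per group. Dividing by 0.9 for dropout gives 50 per group, or 100 in total, as stated. Nothing below depends on it.

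**The two windows in days.** Inputs: Day 0 baseline, first dose the next day, baseline within 60 days of consent, week 24 at Day 168 (all section 4.1). Three months is taken as 90 to 92 days.

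| | Earliest scan | Latest scan |
| --- | --- | --- |
| Footnote 17, read literally | 90–92 days before Day 0 | 90–92 days after Day 0 |
| Section 4.3 note | up to 60 + 90 = 150 (60 + 92 = 152) days before Day 0 | Day 0 |

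- Late end: 90/168 = 54% and 92/168 = 55% of the treatment period, past the Day 84 visit. From such a scan only 168 − 92 = 76 to 168 − 90 = 78 days remain to Day 168.
- A scan on Day 60 satisfies footnote 17 and fails section 4.3.
- A scan 120 days before Day 0, in a patient who consented 60 days before Day 0, satisfies section 4.3 and fails footnote 17. Reading footnote 17 as looking backward only would remove the first conflict but not this one.

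**Effect on the estimate if a post-dose scan is used.** Let Δ be the true week-24 difference, f the share of echo patients in each arm with a post-dose baseline, g the fraction of Δ already present at that scan, and b the slope of the week-24 value on the baseline value. The arms then differ at the recorded baseline by f·g·Δ.

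- Unadjusted change score: Δ − f·g·Δ = Δ(1 − f·g).
- Planned model, adjusted for baseline: about Δ − b·f·g·Δ = Δ(1 − b·f·g).

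The documents give none of f, g or b. All three are assumptions here: f from 0 to 30%, b from 0.5 to 0.8, and g = 0.5. That g corresponds to an effect building linearly and a scan at Day 84 (84/168).

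| f | Loss, unadjusted change (f·g) | Loss, planned model, b = 0.5 | Loss, planned model, b = 0.8 |
| --- | --- | --- | --- |
| 0 | 0% | 0% | 0% |
| 10% | 5% | 2.5% | 4% |
| 20% | 10% | 5% | 8% |
| 30% | 15% | 7.5% | 12% |

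A simulation of the adjusted model agreed with the formula. At f = 20%, g = 0.5 it kept 0.956 (b = 0.5) and 0.919 (b = 0.8) of the effect, against 0.95 and 0.92. With f = 0 it kept 1.00.

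The loss is proportional to g. If the whole effect were present by the time of the scan (g = 1), the top of the range would double to 0.8 × 0.30 × 1 = 24%.

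**The case against.** The strongest reply is that this is loose wording, not a working permission. Footnote 17 nowhere says that a scan after dosing may be used. The protocol elsewhere places baseline before administration, section 4.3 closes the window at baseline, and the correction of the same phrase for UACR and cystatin C suggests that a backward window was meant. Table 1 schedules no echocardiogram between baseline and week 24, so a post-dose baseline would need an unscheduled scan. LVEF must also be recorded for eligibility, from data after consent or within 3 months before it, so a pre-dose LVEF should exist and sometimes a full scan. The share f may well be zero.

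Most of this stands, and it rules out several stronger inferences that a reader might draw.

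- *Part of any cardiac effect is subtracted.* This happens only if a post-dose scan is actually used, and the documents do not show that one was.
- *Fallback use must be common because the echocardiogram is optional ("16) This is an optional item").* Optional status says nothing about how often a fallback is used, and using a fallback is not the same as using a post-dose one.
- *The loss is 5 to 15%.* That is the unadjusted change score at f = 10 to 30%. The planned model adjusts for baseline and loses less, and zero belongs in the range.
- *A five-month-old pre-dose scan biases the result.* The arms are randomised and blinded, so drift before dosing is expected to be equal in both and cancels in the difference. An older scan costs precision only.

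The reply does not remove the conflict. The two windows still disagree at the early end on the kindest reading, and nothing in the SAP enforces the kind reading at the late end. The eligibility record covers LVEF, not necessarily e′, E/e′, LVMI, LAD or LAVI.

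**Conclusion.** The point holds as an internal inconsistency of minor importance. The textual conflict is certain. Its consequence is conditional: if post-dose scans served as baselines, attenuation in the planned model would be about 0 to 12%, under the assumed share of 0 to 30%, half of the effect already present, and a slope of 0.5 to 0.8. The true figure cannot be derived from the documents.

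The reach is narrow. The echocardiographic measures are optional, sit among the other endpoints, and are described as an exploratory evaluation of cardiac function. The SAP bases the efficacy conclusion on CAVI in the FAS. A reader might infer that the trial's main result is touched; it is not, and neither are UACR, safety or the sample size. Footnote 7 shared the wording but was corrected in version 1.2.

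**What to change.** Bring footnote 17 into line with the section 4.3 note, so that both state one window and only an echocardiogram obtained on or before Day 0, before the first dose, can serve as baseline. There is no need to narrow the early end: keeping section 4.3's lower limit retains scans made for eligibility.

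In the SAP, under data handling, add a date check applied alike to both arms: any baseline echocardiogram dated after the first dose is treated as missing. The check can also be run on data already collected, and the number of affected patients per arm reported. If it is zero, the question of attenuation is closed.

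The cost is one sentence in the protocol and one date comparison in the SAP. A few patients may lose their echo baseline. Because the SAP does not impute missing values, they would drop out of the baseline-adjusted echocardiographic models.
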